### Measures

#### Outcome Measures

##### ART Adherence

ART adherence is assessed using both Wisepill (primary) and biomarker (secondary) over 12 months. Wisepill is a real-time electronic adherence monitoring device that sends a cellular signal to the Wisepill data server each time the device is opened. The data can be accessed via an online dashboard where the date and time of all doses are recorded. Participants are instructed to put their ART medication in the Wisepill device and regularly charge the device. Reminder calls are also conducted at regular intervals (2, 5, and 10 months) to remind participants to continue to use and charge the device. ART adherence data are calculated as the percentage of prescribed ART taken over the 12-month period.

DBS is used as the secondary measure of ART adherence. DBS is collected by spotting 50 μL of blood on a Whatman 903 protein saver card and stored at −80 °C temperature to later perform tenofovir diphosphate assays (TFV-DP). TFV-DP is a biomarker reflecting cumulative ART adherence in the preceding 6‐8 weeks. TFV-DP has a half-life of approximately 17 days. As not all participants are required to be on a TFV-DP regimen, this will be for a subsample (approximately 94% of participants reported taking TFV-DP at baseline), though analysis by DBS will allow for a gross confirmation that at least some recent ART is present in the system for the majority of participants [59,60]. TFV-DP testing is conducted at the University of Cape Town (UCT) laboratories.

##### Substance Use

The primary assessment of substance use is urinalysis (Medical Diagnostech rapid detect 6-panel urine test for delta-9-tetrahydrocannabinol [cannabis], methamphetamine, amphetamines, opiates, cocaine, and methaqualone), collected at baseline and at 1-, 3-, 6-, and 12-month follow-ups. As a supplemental biomarker assessment of alcohol, we are assessing phosphatidylethanol (PEth), a biomarker of alcohol use. PEth is a biomarker that is only produced in the presence of alcohol, which has high sensitivity and specificity for detecting alcohol use among people with HIV [61]. PEth can detect alcohol use in the past approximately 21 days [19]. PEth testing is also conducted using DBS with 50 μL of blood spotted on a Whatman 903 protein saver card. PEth samples are shipped to the United States, and testing is being conducted by the US Drug Testing Laboratories.

Self-reported substance use is also assessed at the same time points as a secondary outcome using the WHO ASSIST [31], which was developed by the World Health Organization to detect and manage substance use and related problems in primary and general medical care settings. The test assesses risk for alcohol, cannabis, cocaine, opiates, amphetamines, hallucinogens, and other drug-related problems in primary care and has been validated in South Africa [62]. It categorizes individuals into low (≤3 for drugs; ≤10 for alcohol), moderate (4‐26 for drugs; 11‐26 for alcohol), or high risk (>26 for all) for substance use–related problems. The WHO ASSIST is administered at screening and 3-, 6-, and 12-month assessment time points.

##### HIV Viral Load

HIV viral load is assessed at baseline and at 3-, 6-, and 12-month follow-ups. If viral load results are not available within 30 days of each study assessment on the patient’s clinic chart with the participant’s consent. If results are also not available in the national database, participants will undergo a blood draw for viral load assay by a trained study nurse. Viral load testing is conducted by the National Health Laboratory Service in Cape Town, South Africa, using the Abbott Alinity m HIV-1 Viral load assay (Alinity). We will assess the percentage of the sample with detectable viral load. This assay detects viral load with a lower limit of quantification of 50 copies/mL [63-65].

### Implementation Outcomes

#### Uptake

Uptake will be measured by patient participation and retention. We will assess the percentage who agree to enroll in both conditions and treatment attendance for both *Khanya* and ETAU participants. We will compare the demographic and clinical characteristics of individuals who initiate treatment and are retained compared to all eligible patients.

#### Acceptability and Feasibility

Guided by RE-AIM, the Applied Mental Health Research Group implementation outcome assessment [66] assesses acceptability (ie, tolerability or satisfaction of a proposed intervention for a particular setting) and feasibility (ie, extent to which the intervention can be implemented as intended in a given setting) of *Khanya*. This assessment was adapted from the pilot and is given to all participants randomized to *Khanya,* regardless of step-up, at the 3-month follow-up. A subset of individual, in-depth, semistructured interviews are also being conducted to evaluate participant perceptions of the *Khanya* intervention.

#### Fidelity

All *Khanya* sessions are audiotaped, and 20% (randomly selected) are reviewed by a trained, independent assessor who rates both adherence to and competence in delivering intervention content based on procedures developed in the pilot [19]. For adherence to intervention content, we are using an adapted rating checklist for peer interventionists to determine whether the specific treatment components were delivered. Following recommendations for implementation science research [67], a “fidelity score” is calculated based on the proportion of key intervention components delivered as intended across sessions. For competence in delivering the intervention, the independent assessor rates general clinical skills (eg, empathic listening and nonjudgment) using the Enhancing Assessment of Common Therapeutic Factors (ENACT) [68], a cross-cultural assessment of lay provider competence in delivering behavioral interventions.

### Economic Evaluation Outcomes

#### Intervention Costs

The resources required to implement and sustain each step of *Khanya* in the clinic setting will be identified through a site-specific microcosting analysis, guided by a tailored version of the Drug Abuse Treatment Cost Analysis Program instrument [69]. Data are obtained using a combination of a site visit with semistructured interviews and administrative data. Resources will be valued using nationally representative unit costs [70].

#### Health Care Resource Usage

Usage of health care resources beyond the intervention will be self-reported using time-anchoring methodology via the Nonstudy Medical and Other Services (NMOS) form [71]. This information is measured for the 30 days prior to baseline, then “since the last assessment” at 3-, 6-, and 12-month follow-ups.

#### Other Resource Usage and Employment

Societal factors such as employment, school/workplace productivity, travel time to care, caregiver burden, and criminal activity are also self-reported using the NMOS. Employment is assessed as working full-time, working part-time, unemployed or laid off and looking for work, in school or training, retired, disabled, and in the military at all major visits.

#### Health-Related Quality of Life

Health-related quality of life (HRQoL) is measured using the EuroQol-5D (EQ-5D), the most widely used of the major instruments capable of calculating a generalizable health utility index value to calculate quality-adjusted life-years (QALYs); it is also among the most sensitive to changes in pain, and physical- and mental-health functioning [72]. The EQ-5D measures HRQoL across 5 dimensions (mobility, self-care, usual activities, pain/discomfort, and anxiety/depression), via 5 levels (no problems, slight problems, moderate problems, severe problems, and extreme problems). The EQ-5D has health utility value sets representing the preferences of the general populations of many countries, including in Africa. HRQoL is collected at all major time points, alongside the NMOS.

### Research Assistant Training

All research assistants regularly complete Good Clinical Practice trainings through the CITI Program (Collaborative Institutional Training Initiative) before study initiation and throughout the trial [73]. They also received in-depth training from project directors on all data collection instruments, the use of REDCap, and the use of Wisepill. Standard operating procedures for informed consent, maintaining confidentiality, data management, adverse events, providing referrals, collecting dried blood spots and urine samples, and conducting medical chart extraction are reviewed by all members of the research team.

### Peer Interventionist Training

Peer interventionist training was delivered over approximately 3 days, with ongoing weekly supervision and booster training over 1 month. Peer training includes basic counseling and peer recovery training, HIV psychoeducation and adherence counseling training, and *Khanya* intervention–specific skills, including motivational interviewing, problem-solving, behavioral activation, and mindfulness-based relapse prevention. Training included both in-person and virtual components. Initial training in basic counseling skills and intervention-specific skills, such as behavioral activation and problem-solving, was facilitated by a clinical psychologist and psychiatric nurse at UCT. Motivational interviewing training sessions were conducted by a clinical psychologist and peer interventionist at the University of Maryland virtually, with additional support from a peer based in South Africa who delivered the intervention in the pilot. The interventionists also attended an advanced HIV counseling course offered in the HIV Mental Health Research Unit at UCT.

Peer training included sharing of personal lived experience with a peer supervisor, guiding principles of recovery, motivational interviewing, principles in the peer role, stages of change, and setting boundaries in counseling. Interventionists engaged in role-plays of *Khanya* sessions with the local clinical psychologist, who provided feedback before moving on to subsequent sessions. The interventionists also assisted each other with role-plays as a way of peer tutoring/training.

The readiness of the peer interventionist to deliver the intervention was assessed through the rating of the first 3 sessions using the ENACT to measure therapeutic competency [68]. ENACT findings were discussed by the training team to assess and confirm interventionist readiness for session delivery.

### Peer Interventionist Supervision

Throughout the study, the two peer interventionists receive weekly supervision from a local bilingual (English and *isiXhosa* speaking) clinical psychologist in South Africa and support from a US-based peer recovery specialist with relevant lived experience and training in peer recovery in the United States. The interventionists discuss their current caseload and any questions or concerns they have about how to best support each participant. This also provides an opportunity for interventionists to receive support from the clinical psychologist around their own mental health and workload. Supervision includes ongoing training of the intervention material, along with any additional information that might pertain to a specific participant’s case where support is needed. This allows for continued honing of intervention delivery skills and equips peers with additional knowledge to help navigate future scenarios with participants. The clinical psychologist also checks for fidelity and compliance with ethics requirements while also encouraging peer-to-peer support for participant cases and personal well-being. Immediate support for interventionists to debrief with a second clinical psychologist after sessions involving severe risk and distressed participants is also provided.

### Power Calculation and Sample Size

The main analysis on which the sample size calculation for the effectiveness analysis was based is the effect of the *Khanya* intervention versus ETAU on ART nonadherence measured using weekly Wisepill data over 12 months. Our pilot data that compared *Khanya* to ETAU at 3 months revealed a large effect size (*d*=1.02) on ART adherence in favor of the *Khanya* intervention. However, given that effect size estimates generated from pilot data using small samples are highly variable and imprecise [74], we expect the true effect size may be smaller or larger than the one observed in our pilot study. Furthermore, we anticipate a slightly smaller effect size in the study because we will assess our primary outcome over 12 months (rather than 3 months in the pilot) and not all patients will receive the full *Khanya* package. Based on our pilot data, after 1 month, we expect only ~56% of participants would need to be stepped up to the second step of the intervention. Accounting for a conservative anticipated effect size estimate of 0.5 (moderate) and an attrition rate of 20% at 12 months, we will have over 0.8 power to detect a difference in ART adherence between groups at 12 months with our sample size of 160.

### Data Management and Data Analysis

#### Quantitative Data

Trained research assistants are administering all assessments in private rooms adjacent to the clinic and collecting data using REDCap. In the REDCap database, participants are identified only by participant number and date [75]. The document linking participant names to participant ID numbers is stored on a password-protected secure server only accessible by the local research team. Once collected, all data are reviewed twice for quality assurance including checking consistency of participant responses, ensuring that reported values fall within the range of possible values, and flagging any missing values. Wisepill data are initially stored on the online Wisepill server and then imported to REDCap. Wisepill devices are checked weekly on the server to ensure devices are operational. All data are backed up on a weekly basis. All data management procedures are outlined in the study team’s internal data management standard operating procedure document and in the trial’s Data Safety Monitoring Plan.

#### Qualitative Data

All semistructured interviews are audio-recorded, and audio files are only saved using participant number and date. The document that links participant names to ID numbers is stored on a password-protected secure server accessible only by the local research team. Interviews are translated from *isiXhosa* to English and reviewed twice for quality assurance, including the removal of any potentially identifiable information. Interview audio files are stored in the Study Box folder that is hosted by the University of Maryland and is only accessible by study team members. Translated audio files are also imported to Rev, a secure, encrypted transcription software program [76]. In Rev, the translated audio files are generated into a written transcript. These transcripts are reviewed twice by separate trained research assistants for quality assurance. Once uploaded to Rev for transcription, audio files are immediately deleted from the digital recorder. Recordings will be maintained until 7 years after the publication of study results, as per the guidelines of the American Psychological Association [77].

#### Biological Samples

Biological samples are stored using participant ID numbers that do not contain any identifying information. Only trained researchers have access to these samples when they are in storage, and only professional lab technicians have access to these samples while testing. All samples will be shipped and/or destroyed within 5 years after the study is complete. For urinalysis testing, once the sample has been collected and the panel test has been processed, the results must be taken within 5 to 10 minutes of sample collection. The participant ID number is written on the panel, and two photos of the results are taken and uploaded to a secure study drive for later data entry. The urine sample and panel are disposed of and the work station is sanitized.

#### Effectiveness Outcome Analyses

Quantitative longitudinal analysis will evaluate the effectiveness of the *Khanya* intervention package (including individuals who have received either step 1 or 2) compared to ETAU on effectiveness outcomes over a period of 12 months. We will calculate descriptive statistics on all outcome variables (eg, mean, SD, and range). To reduce bias and improve accurate estimation of the intervention effects, we will conduct all analyses according to the intent-to-treat principle, such that all participants are analyzed based on their initial randomization assignments regardless of subsequent participant dropout or missing data.

For the continuous primary outcome of percentage ART adherence over the past week (doses taken vs prescribed, measured weekly) using Wisepill, provided distributions are appropriate and assumptions are met, we plan to fit a linear mixed model to evaluate the intervention effect, time effect, and intervention by time interaction. This model will allow for the inclusion of both random and fixed effects. The restricted maximum likelihood method will be used to estimate the model parameters. Wald tests will be used to test the statistical significance of these parameters. The intervention effects (*Khanya* vs ETAU) will be compared at the 1-, 3-, 6-, and 12-month follow-up assessments, including the potential differential trajectories between treatment groups. We will use nonparametric techniques like locally estimated scatterplot smoothing to model the best-fitting trajectory, allowing for linear, piecewise, or any higher-ordered patterns as supported by the data. We will consider theoretically relevant baseline covariates in the models (eg, demographic and/or clinical characteristics). All other continuous outcomes will be modeled using a similar approach, incorporating all major assessment time points. Binary outcomes (eg, urinalysis and viral load) will be modeled using a generalized linear mixed model. We will use a penalized quasi-likelihood method to estimate the parameters in the model, and the Wald test will again be used to test the significance of these parameters.

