## Methods

### Setting

All participants (n=160) are being recruited from two primary health care clinics located in the periurban suburb of Khayelitsha, situated on the outskirts of Cape Town, South Africa, which has the highest HIV prevalence in South Africa’s Western Cape [26,27]. The population of Khayelitsha is predominantly Black African and *isiXhosa* speaking. All study materials are translated into *isiXhosa* and back-translated into English to ensure all materials delivered in *isiXhosa* are accurate to the original English versions. The primary health care clinics have HIV and tuberculosis services integrated into primary care and are publicly funded. In Khayelitsha, there is a freely available SUD treatment program, Matrix, an evidence-based program run by the City of Cape Town that offers a 16-week rehabilitation focused on cognitive-behavioral strategies to support early recovery and relapse prevention [28-30], which is colocated at one of the primary health care clinics.

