### Study Procedures

After participants provide informed consent, they are invited to complete a baseline assessment, which includes a battery of self-report assessment measures related to psychosocial status, HIV infection history, ART adherence, and current and past SUD, along with biological measure sample collection. At the baseline visit, participants in both conditions are provided with a Wisepill device for real-time, wireless, electronic adherence monitoring [32,33]. The 2-week period between baseline and randomization serves as the baseline Wisepill assessment, and Wisepill adherence monitoring is continued over 1 year.

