## Results

This study presents a protocol for a hybrid type 2 effectiveness-implementation randomized controlled trial testing the stepped-care approach of a peer-delivered behavioral activation intervention for people with HIV with concurrent SUD. Funded in August 2022, recruitment for the trial began in June 2023 and primary data collection is projected to be completed in February 2027. Recruitment for the clinical trial (n=162) was completed in March 2026. It is expected that all analyses will be complete by December 2027.

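### The primary model gives no stated role to the 2-week pre-randomisation Wisepill baseline; committing to it would cost nothing and could add precision

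*Protocol article*

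**What the plan says.** Under Study Procedures, both arms receive a Wisepill device at the baseline visit, and "The 2-week period between baseline and randomization serves as the baseline Wisepill assessment". The Randomization section gives this measurement as the reason for the 2-week delay before allocation.

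Under Effectiveness Outcome Analyses, the primary outcome is the weekly percentage of prescribed doses taken. The planned analysis is a linear mixed model fitted by REML with Wald tests, and the terms named are intervention, time and intervention by time. The arms are to be compared at 1, 3, 6 and 12 months. The only sentence on covariates is "We will consider theoretically relevant baseline covariates in the models (eg, demographic and/or clinical characteristics".

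Other continuous outcomes follow a similar approach using all major assessment time points. The account of chart extraction under Follow-Up Assessments counts baseline among the major visits.

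Power Calculation and Sample Size assumes a standardised effect of 0.5 and the loss of one participant in five by the last follow-up. Its claim is: "we will have over 0.8 power to detect a difference in ART adherence between groups at 12 months with our sample size of 160". It takes no credit for a covariate.

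**The concern.** A baseline on the same device as the primary outcome, taken in everyone before allocation, is an obvious candidate predictor of later adherence. The article fixes the main terms and the estimation method but leaves open whether this measurement enters the model, and how.

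Three analyses fit the text: ignore the baseline weeks, use them as a covariate, or include them as outcome rows. They differ in precision. If the baseline weeks become outcome rows and the arms' baseline means are left free, the treatment contrast becomes a difference in change, which can be less precise than ignoring baseline altogether. In that coding, an averaged intervention term would also mix in a pre-treatment difference.

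The gap matters more because the stated power is close to 0.80 on the article's own inputs.

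**Working it through.** **Inputs from Power Calculation and Sample Size:** N=160, d=0.5, attrition 20%. Allocation is 1:1 (Randomization).

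**Assumptions:** two-sided 5% (alpha is not stated); standardised outcome with SD 1 and equal baseline and follow-up variances; correlation r between baseline and 12-month adherence (not given, so a range is shown).

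**Step 1: reproduce the stated power.** 160 × 0.8 = 128 completers, 64 per arm. An unadjusted two-sample t-test at d=0.5 gives 0.801 (0.807 by normal approximation), which agrees with the claim of over 0.8. The t-test needs 64 per arm, and 128/0.8 = 160 exactly. At 63 per arm power is 0.795.

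**Step 2: baseline as a covariate.** Residual variance is multiplied by 1−r², so effective d = 0.5/√(1−r²). The equivalent number of unadjusted completers is 128/(1−r²).

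| r | 1−r² | effective d | power | 128 completers act like |
|---|---|---|---|---|
| 0 | 1.00 | 0.500 | 0.801 | 128 |
| 0.1 | 0.99 | 0.503 | 0.805 | 129 |
| 0.2 | 0.96 | 0.510 | 0.817 | 133 |
| 0.3 | 0.91 | 0.524 | 0.837 | 141 |
| 0.5 | 0.75 | 0.577 | 0.900 | 171 |
| 0.6 | 0.64 | 0.625 | 0.939 | 200 |

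**Step 3: baseline as an unconstrained outcome, testing change.** As a simple change-score approximation, the variance is 2(1−r) and effective d = 0.5/√(2(1−r)).

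| r | 2(1−r) | effective d | power |
|---|---|---|---|
| 0.3 | 1.4 | 0.423 | 0.660 |
| 0.5 | 1.0 | 0.500 | 0.801 |
| 0.6 | 0.8 | 0.559 | 0.881 |

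Since 2(1−r) − (1−r²) = (1−r)², which is never negative, the covariate analysis is never less precise than the change test under these assumptions. At r=0.3 the gap is 0.837 − 0.660 = 0.177.

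**Step 4: chance imbalance.** With 80 per arm, the standard error of the baseline difference is √(2/80) = 0.158 SD. An imbalance of that size would shift an unadjusted 12-month difference by r × 0.158, or 0.079 SD at r=0.5. Covariate adjustment removes this shift.

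**Step 5: clinic.** If clinic explained 1%, 2% or 5% of the variance (assumed), power would move from 0.801 to 0.805, 0.809 or 0.821.

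**The case against.** The strongest reply is that this is a condensed article. A covariate list is commonly left to the full protocol or analysis plan, and baseline adherence can fairly be read as a clinical characteristic. That largely stands. A reader might infer that baseline adherence has been left out and precision is being given up. The text does not support that: its examples are only examples, and adjustment may already be planned. What remains is that the article specifies the model, gives the 2-week run-in no role in it, and leaves covariates to be considered.

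A reader might also infer that the trial has no power margin. That holds only for an unadjusted t-test at exactly 20% attrition. The article calls d=0.5 conservative against a pilot value of 1.02. It also states "Recruitment for the clinical trial (n=162) was completed in March 2026", and the Discussion cites pilot retention above 90%. With 162 recruited and 10% attrition (about 72 to 73 per arm), the same test gives about 0.85.

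Nor does the text show that the treatment effect would absorb a pre-treatment difference. That depends on a coding choice the article does not describe, and the stated comparisons are all at follow-up times after randomisation.

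The correlation is assumed, and at 0.1 or 0.2 the gain is negligible. The calculation is for a single time point, whereas the primary model uses weekly repeated measures. Both objections stand and limit what the figures can show.

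The absence of a clinic term is weak as a criticism. The Matrix programme is one "which is colocated at one of the primary health care clinics", but facilitated referral to it is offered in both arms, so colocation does not by itself create an arm difference. No stratification is described that would require the term.

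**Conclusion.** The point holds as an efficiency recommendation. The plan collects a pre-randomisation value of its primary outcome and does not say how the primary model uses it. The unadjusted comparison is valid, so no bias is being corrected.

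For the powered 12-month contrast, using the baseline as a covariate moves power from 0.80 to between about 0.82 (r=0.2) and 0.94 (r=0.6). An unconstrained change test would lower it to about 0.66 at r=0.3. These figures rest on d=0.5, 64 per arm, two-sided 5%, equal variances and an assumed correlation. They illustrate the direction and possible size of the effect; they do not give the power of the weekly mixed model, for which the article supplies no inputs.

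**What to change.** State in the analysis section, before final analysis, that the primary model takes post-randomisation weeks as outcomes and includes the 2-week baseline Wisepill percentage as a fixed covariate. Alternatively, keep the baseline in the outcome vector and constrain its mean to be equal across arms; this also retains participants whose baseline Wisepill data are missing. Handle the baseline value of each other effectiveness outcome the same way (urinalysis, PEth, WHO ASSIST, TFV-DP, viral load), with the covariate form for the binary outcomes. If an existing analysis plan already says this, a sentence referring to it is enough.

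A fixed effect for clinic is an optional minor addition.

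The cost is one or two sentences and one or two degrees of freedom. It needs no new data and no change to trial procedures. Primary data collection is projected to run to February 2027 and analyses to December 2027, so there is time to settle it.
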